### **3.3.3.3 Substudy I: Prospective validation of the IMPROVE bleeding risk score**

TPX related-bleeding risk assessment in medical inpatients is a challenge. The IMPROVE bleeding risk score consisting of 11 demographical, clinical, and laboratory items was derived and validated to predict in-hospital bleeding in medical inpatients upon admission. However, in the external validation cohort, bleeding as the main outcome was retrospectively identified based on ICD-10 codes of major bleeding, resulting in limited accuracy of the outcome measurement. In addition, potentially relevant non-major bleeding events were missed. Thus, external validation with prospective and accurate assessment of bleeding outcomes has not been performed yet, and whether this model ([www.outcomes-umassmed.org/improve/](http://www.outcomes-umassmed.org/improve/)) may help to adequately assess the risk of bleeding prior to TPX prescription remains to be evaluated.

We aim to prospectively validate the IMPROVE bleeding risk score in this Swiss cohort of hospitalized medical patients. In addition, we will review prophylaxis practice patterns and assess the effects that various prophylactic regimens have on the risk of bleeding and the performance of the score. Finally, we will calculate the IMPROVE VTE risk score in addition to the IMPROVE bleeding risk score to assign a risk-benefit category to all patients in our cohort.

### **3.3.3.4 Substudy II: Correlation between nurses' estimation of mobility and an objective motion measurement**

VTE RAMs for inpatients frequently include immobilization as a variable. However, the reliability and inter-individual variability of this assessment by nurses or doctors is not well established. The Braden scale has been validated to identify hospitalized patients at risk of pressure sores (**Figure 3**). This scoring system includes 6 items with a total score ranging from 0 to 23. Patients with a score of 9 or less are considered at very high risk. Two items of this score are specifically dedicated to assess surrogates of physical activity: Activity and Mobility with scores ranging from 1 to 4. We will evaluate the correlation between two items dedicated to mobility in the systematically documented Braden scale among internal medicine patients. In case of good reliability of either or both items, these variables which are already systematically documented by nurses could be integrated to VTE RAMs to identify patients warranting thromboprophylaxis.

Prognostic values on LOS, readmission, transfer to post-acute care facility of accelerometer-measured and nurses' estimation of mobility will be assessed.

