### 3.3.3.2 Mobility measurements

Because immobilization criteria defined in each RAM consider the patient's ability or inability to move and its duration (**Table 1**), we will objectively assess periods of mobility in all eligible and consenting patients using a wrist-worn tri-axis accelerometer (GENEActiv Original, ActivInsights Ltd, UK, <https://www.activinsights.com/actigraphy/geneactiv-original/>), parametrized at 50 Hz. These accelerometers have been shown to provide a reliable and valid measurement of physical activity in adults and hospitalized patients. The devices will be provided to the patients immediately after inclusion and patients will choose on which wrist they prefer to wear the device. Previous studies have shown that measuring site does not influence measurement. Patients will be asked to wear the device continuously (day and night, including showering) until hospital discharge or transfer to another department (e.g. intensive care, surgery unit). Accelerometry data will be extracted and analyzed using the GGIR package for R (version 1.11 or later). A valid day will be defined as at least 10 hours of daytime wear, and at least 24 hours of valid data will be required for analysis. In the analysis, we will consider the following measurements: minutes/day in different type of activities, no activity or sleep; total minutes during day spent active/inactive; mean acceleration in miliG/vector.

Physical activity raw data will be further processed using the open source GENEAcclassify R-package (<https://cran.r-project.org/web/packages/GENEAcclassify/GENEAcclassify.pdf>) in order to obtain the number of steps taken per day, the mean cadence, and the maximum gait speed (m/s). We will estimate the percentage of time of patient's mobility, using a cut-off of <4 steps and ≥4 steps taken per minute to define periods of immobilization and mobilization respectively, as previously reported in a study of medical inpatients.

At baseline, patients will be asked about their ability to walk, i.e. whether they are able to walk independently, with assistance from one or two persons, with or without mobility aids, or if they are not able to walk. In addition, we will assess from medical records whether physical therapy has been prescribed for mobilization.

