| 15-18 Low Risk, 13-14 Moderate Risk, 10-12 High Risk, >9 Very High Risk                  |                                                    |                                                                      |                                                                        | TOTAL |

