|  | 
a) demographic data;
 
b) all items of the simplified and original Geneva score, IMPROVE score, and Padua score, and other potential VTE risk factors
 
c) comorbidities
 
d) potential contraindications to pharmacological TPX
 
e) laboratory findings that are relevant concerning VTE and bleeding risk
 
f) medications at admission with a potential antithrombotic effect
 
g) treatments during the current hospital stay
 
h) information on patient's autonomy (modified Barthel Index)
 
i) patient's ability to walk
 
j) risk of pressure sores (Braden scale)
 
Data will be collected from electronic health records, except for information such as contact details, mobility, paresis/paralysis, recent travel, dehydration, leg edema, patient autonomy, and ability to walk, which will be collected at the patient bedside (from the patient and/or nurse in charge) by trained study nurses.
 
In addition, objective mobility data will be measured continuously for the duration of hospital stay using a wrist-worn tri-axis accelerometer (GENEActiv Original, ActivInsights Ltd, UK).
 
On the second day of admission, study nurses will ask the treating physicians to judge whether their patients fulfill the different immobilization criteria, and to subjectively estimate the patient's mobility level in standardized terms.
 
Prior to discharge (1 day prior or day of discharge) the discharge location, length of stay, medical outcome events (HA-VTE, all-cause death, major bleeding, clinically relevant non-major bleeding), and treatments since admission will be obtained from medical records and/or interview of the participant and treating health care personnel. Autonomy will be assessed using the modified Barthel Index.
 
To assess outcome events, participants will be followed with a follow-up phone call 90 days after enrolment.
 
Substudies
 
Prospective validation of the Improve bleeding risk score
 
The IMPROVE bleeding risk score consisting of 11 demographical, clinical, and laboratory items was derived and validated to predict in-hospital bleeding in medical inpatients upon admission. All variable for the score will be collected at baseline. We aim to prospectively validate the IMPROVE bleeding risk score in this Swiss cohort of hospitalized medical patients.
 
Correlation between nurses' estimation of mobility and an objective motion measurement
 
The Braden scale has been validated to identify hospitalized patients at risk of pressure sores. This scoring system includes 6 items with a total score ranging from 0 to 23. Two items of this score are specifically dedicated to assess surrogates of physical activity: Activity and Mobility with scores ranging from 1 to 4. We will evaluate the correlation between two items dedicated to mobility in the systematically documented Braden scale among internal medicine patients. In case of good reliability of either or both items, these variables which are already systematically documented by nurses could be integrated to VTE RAMs to identify patients warranting thromboprophylaxis.
 
Feasibility of a future randomized controlled trial
 
In a subset of 100 patients the recruitment feasibility for a future randomized controlled trial comparing different VTE prevention strategies will be assessed. Patients who are at high risk of HA-VTE as identified
 |

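### Substudy II: the analysis sentence correlates two Braden items with each other and leaves out the accelerometry comparator that the heading promises

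*Protocol*

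**What the plan says.** The heading of Protocol section 3.3.3.4 sets the aim: "Correlation between nurses' estimation of mobility and an objective motion measurement". After introducing the Braden scale and its Activity and Mobility items (each scored 1 to 4), the section states the analysis: "We will evaluate the correlation between two items dedicated to mobility in the systematically documented Braden scale among internal medicine patients". The synopsis (Measurements and procedures, Substudies) carries the same heading and the same sentence.

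The consequence drawn is: "In case of good reliability of either or both items, these variables which are already systematically documented by nurses could be integrated to VTE RAMs". Section 3.3.3.4 then adds a separate analysis, absent from the synopsis: "Prognostic values on LOS, readmission, transfer to post-acute care facility of accelerometer-measured and nurses' estimation of mobility will be assessed".

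On data, section 3.3.3.2 says "we will objectively assess periods of mobility in all eligible and consenting patients using a wrist-worn tri-axis accelerometer". Table 3 schedules the Braden scale once, at the baseline visit (d0).

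On the instrument, section 3.3.3.4 and the synopsis say "This scoring system includes 6 items with a total score ranging from 0 to 23". Section 3.3.3.4 also says "Patients with a score of 9 or less are considered at very high risk", whereas the foot of the printed Braden figure reads "15-18 Low Risk, 13-14 Moderate Risk, 10-12 High Risk, >9 Very High Risk".

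**The concern.** The sentence that defines the correlation names a pair of variables, and it is not the pair in the heading. Both named variables are nurse ratings from one scale. Their correlation says how closely two parts of that scale move together. It says nothing about whether either part follows measured movement, which is the declared question.

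This is not detail left to a statistical analysis plan. The protocol does state which variables are to be correlated, so a later plan that followed it faithfully would inherit the wrong pair. The sentence also leads to a suggestion that the items might enter VTE risk assessment models, and readers may give the coefficient more weight than it can bear.

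**Working it through.** **1. Aim and analysis compared**

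| Place | Nurse rating | Objective motion |
|---|---|---|
| Heading, section 3.3.3.4 and synopsis | yes | yes |
| Correlation sentence, section 3.3.3.4 and synopsis | both Braden items | not named |
| Prognostic sentence, section 3.3.3.4 | yes | yes, but for length of stay, readmission and transfer |
| Section 4.1.2, work package 2 | Braden items not named; the subjective measure is physician perception | yes |

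No row other than the heading pairs the Braden items with accelerometry for a correlation.

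**2. What the literal analysis yields.** Two variables give one coefficient. The next sentence speaks of either or both items performing well. Judging the items one by one needs at least two coefficients, each against an outside reference, and a single inter-item coefficient cannot separate them. Nor can it measure reliability in the repeat-rating sense, because Table 3 schedules one rating per patient.

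**3. Whether the data allow the intended analysis.** The Braden scale is recorded at d0. The accelerometer is handed out immediately after inclusion and worn until discharge or transfer (section 3.3.3.2). The same patients therefore have both measurements, and they start together. Section 3.3.3.2 lists several candidate outputs, including steps per day, mean acceleration and the percentage of time mobile, defined by 4 or more steps per minute. Substudy II names none of them.

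**4. Link to VTE.** The prognostic outcomes in section 3.3.3.4 are length of stay, readmission and transfer. HA-VTE is not among them. Expected HA-VTE events at the rates in section 4.1.1 (67% of patients at 2.8%, 33% at 0.6%, N = 1350):

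- overall risk = 0.67 × 0.028 + 0.33 × 0.006 = 0.01876 + 0.00198 = 0.02074
- events = 1350 × 0.02074 = 28.0

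**5. Braden total, from the printed scale.** Five items run 1 to 4 and one (friction and shear) runs 1 to 3.

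- minimum = 6 × 1 = 6; maximum = 5 × 4 + 3 = 23
- attainable totals = 23 − 6 + 1 = 18

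The stated upper bound of 23 reproduces. The stated lower bound of 0 does not.

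**6. Very-high-risk band.** The text's version covers 6 to 9 and does not overlap the printed bands 10–12, 13–14 and 15–18. The figure's >9, read literally, covers 10 to 23, which is 14 of the 18 totals. It overlaps all three printed bands and leaves the 4 totals from 6 to 9 without a label.

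**The case against.** The strongest reply is that the sentence is elliptical and that its surroundings supply the comparator. The heading names it, the either-or-both wording makes sense only against an outside reference, and the section closes by mentioning accelerometer-measured mobility. This stands as evidence of intent, and it is why the point is a drafting error. It does not make the stated analysis correct: the defining sentence appears twice, omits the comparator both times, and no other section repairs it.

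It is also fair to say that the choice of coefficient and accelerometry window could be left to a statistical analysis plan. Their absence alone is not the complaint. Since the sentence must be rewritten anyway, naming them there is convenient.

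A reader might infer several stronger things that the documents do not support:

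- That the substudy cannot answer its question. It can, because both measurements are collected in the cohort.
- That the whole substudy is affected. The prognostic analyses name both measures and stand as they are.
- That the two items will correlate almost automatically because one nurse rates both. The protocol says only that nurses document the items; it does not identify the rater and gives no figure for their correlation.
- That there is a binding rule to put the items into risk models. The wording is a prospect, with no threshold or commitment.
- That the Braden range and cut-off errors undermine the result. No planned analysis uses the total or its bands, and the correlation concerns two items scored 1 to 4. The figure's sign may also be a misread ≤ from text extraction.

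**Conclusion.** As written in section 3.3.3.4 and the synopsis, the Substudy II correlation is between two Braden items and omits accelerometry, so taken literally it does not deliver the aim in its heading. The effect is confined to one analysis in one substudy. No primary or secondary objective of the study depends on it, and it is fully repairable from data already planned.

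Once the comparator is named, the result will show how well each item agrees with measured mobility. That alone would not justify adding an item to a VTE risk assessment model, because no association of the Braden items with HA-VTE is planned. Any such analysis would be exploratory: the figure of about 28 events assumes the risks and risk-group split of section 4.1.1 and complete follow-up of all 1350 patients.

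The range error follows from the printed items and is certain. The cut-off conflict depends on whether >9 stands in the source document. Both are clerical and do not carry the point.

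**What to change.** Reword the sentence in section 3.3.3.4 and in the synopsis, for example: the Braden Activity item and the Braden Mobility item will each be correlated separately, by rank correlation, with the percentage of time with at least 4 steps per minute, over a stated window starting at the baseline Braden rating. Another accelerometry measure from section 3.3.3.2 would serve equally well, provided it is named.

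Replace the reference to good reliability with agreement with measured mobility. State that integration into a VTE risk assessment model would also need a shown association with HA-VTE, and that any such analysis here is exploratory.

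As minor corrections, give the Braden total as 6 to 23 in both places, and check the figure's very-high-risk entry against the source so that figure and text agree.

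The cost is wording in two places plus the clerical corrections. No new data, visits or patients are needed. An exploratory HA-VTE analysis, if wanted, adds one model per item.

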### **Figure 3. Braden Scale to predict the risk of pressure sores**

### BRADEN SCALE –Pressure Sore Risk

|                                                                                          |                                                    |                                                                      |                                                                        |              |
|------------------------------------------------------------------------------------------|----------------------------------------------------|----------------------------------------------------------------------|------------------------------------------------------------------------|--------------|
| Sensory perception, ability to respond to pressure related discomfort effectively |                                                    |                                                                      |                                                                        |              |
| 1. Completely limited: Unresponsive                                                      | 2. Very limited: Responds only to painful stimuli. | 3. Slightly limited: Responds to verbal commands, cannot ask to turn | 4. No impairment: no sensory deficit limiting expression of discomfort |              |
|                                                                                          |                                                    |                                                                      |                                                                        | Score |
| Moisture, degree to which skin is exposed to moisture                             |                                                    |                                                                      |                                                                        |              |
| 1. Constantly moist                                                                      | 2. Very moist                                      | 3. Occasionally moist                                                | 4. Rarely moist                                                        | Score |
| Activity, degree of physical activity                                             |                                                    |                                                                      |                                                                        |              |
| 1. Bedfast                                                                               | 2. Chair fast                                      | 3. Walks occasionally                                                | 4. Walks often                                                         | Score |
| Mobility, ability to change and Control Position                                  |                                                    |                                                                      |                                                                        |              |
| 1. Completely immobile                                                                   | 2. Very limited                                    | 3. slightly limited                                                  | 4. No limitation                                                       | Score |
| Nutrition, usual food intake pattern                                              |                                                    |                                                                      |                                                                        |              |
| 1. Very poor                                                                             | 2. Probably inadequate                             | 3. Adequate                                                          | 4. Excellent                                                           | Score |
| Friction and shear                                                                |                                                    |                                                                      |                                                                        |              |
| 1. Problem                                                                               | 2. Potential problem                               | 3. No apparent problem                                               |                                                                        | Score |
| 15-18 Low Risk, 13-14 Moderate Risk, 10-12 High Risk, >9 Very High Risk                  |                                                    |                                                                      |                                                                        | TOTAL |

#### 3.3.3.5 Substudy III: Feasibility of a future randomized controlled trial

In a subset of 100 patients the recruitment feasibility for a future randomized controlled trial comparing different VTE prevention strategies will be assessed. Patients who are at high risk of HA-VTE as identified by the simplified Geneva score and who are meeting the eligibility criteria for this hypothetical randomized trial will be approached at the discharge visit to evaluate acceptability to be enrolled in such a trial.

#### - Inclusion criteria:

- 1) Hospitalized for acute non-surgical illness
- 2) Expected duration of hospital stay  $\geq 48$  hours
- 3) High VTE risk as assessed by the simplified Geneva score ( $\geq 3$  points)

#### - Exclusion criteria

- 1) Known hypersensitivity to heparin
- 2) History of heparin induced thrombocytopenia
- 3) Glomerular filtration rate (GFR)  $< 15$  ml/min
- 4) Platelet count  $< 50,000$  G/L
- 5) Liver failure with spontaneous INR  $> 2.0$
- 6) Active bleeding
- 7) Hemorrhagic transformation of acute ischemic stroke
- 8) Requiring fibrinolysis/thrombolysis within 24h
- 9) Any type of anticoagulation given for  $> 48$ h before baseline inclusion
- 10) Prior hospitalization for  $> 72$ h
- 11) Major surgery within last month, or planned during index hospitalization
- 14) Pregnancy or breastfeeding

The information to assess the eligibility criteria will be collected at baseline.

At the discharge visit, participants who meet these potential trial eligibility criteria will receive oral information regarding a hypothetical randomized placebo-controlled trial comparing pharmacological VTE prophylaxis with enoxaparin 40mg s.c. once daily to placebo s.c. once daily with or without a mobility intervention for the duration of hospital stay until discharge, or for a maximum duration of 14 days. Patients randomized to the placebo group would subsequently be divided into standard care and increased mobility arms. Patient in the increased mobility arms will be asked to walk every day a certain amount of steps, or for those who are unable to walk, to engage in a mobility program which will be done in bed (e.g. three times daily and meals taken out of bed if possible).

Study nurses or investigators will answer questions from potential trial participants, who will then be asked whether they would be willing to provide consent for enrolment in such a trial. In

case they will refuse, the reason for refusal will be assessed as free text. If they would be willing to provide informed consent to participate in the study, patients will then be asked about their preferred follow-up schedule.

We chose the discharge visit to inquire about the potential willingness to participate in a hypothetical trial in order to prevent that TPX provision will be influenced by our study.

